#### Study 2—Cambridge Colour Test

The CCT (Cambridge Research Systems Ltd., Rochester, United Kingdom) will determine chromatic contrast discrimination. The CCT stimulus is a colored Landolt ring displayed within a differently colored background. The position of the opening in the ring is presented randomly in one of four positions; up, down, left, and right. The chromatic contrast of the ring is varied until a threshold is obtained. In our setting, the “ring” will have an opening of 1.25° of visual angle at 3-m viewing distance. To ensure that the break in the ring is identified based only chromatic information, luminance noise is added by subdividing the background and stimulus into small circles randomly varying in size (between 2.8° arcmin and 5.7° arcmin in diameter) and randomly varying in luminance (between 8 and 18 cd/m^2^, in 2 cd/m^2^ of increments). Three different stimuli will be used to measure thresholds along the protan, deutan, and tritan lines of confusion through the background. Thresholds for these three stimuli are determined primarily by the L-, M-, and S-cone, respectively (Regan et al., 1994; Mollon and Regan, 2000). The background is achromatic and located at *u*′ = 0.1977, *v*′ = 0.4689 (CIE 1976 chromaticity diagram). This background will also be used for the Ellipse 1 trial, measuring it with eight vectors. The Ellipse subtest measures the chromatic discrimination ellipse for three different backgrounds, located along the same tritan confusion line; however, in this study, only the achromatic background will be evaluated because of time constraints. The total time to complete both tests is approximately 12 min (6 min each; for more details, see Almustanyir et al., 2020). The CCT represents a cognitively simple test, is easily grasped by individuals, and provides reliable results (Paramei and Oakley, 2014).

### Procedures

It is worth reiterating that different participants will take part in each study. Fifty participants will be randomly allocated to Study 1, and another 50 participants will be allocated to Study 2 (see Figure 1).

#### Study 1—Contrast Sensitivity Function

Before the start of the session, instructions will be provided. The participants will perform a short training with high contrast stimuli at each spatial frequency to familiarize with the procedure and to avoid misunderstanding (part of the light-adapting, see section “Intervention”). Accuracy over speed will be emphasized. The Metropsis software incorporates a check on the validity of the data by using catch trials (suprathreshold stimuli) to minimize random responding.

Measurements will be performed binocularly at a distance of 150 cm from the computer monitor. The participants respond whether the grating is presented on either the left or right side of the computer screen. They will be instructed to respond even if they are not sure. A number of catch trials (commonly used in perception studies to investigate whether or not the participant grasped the task) will be randomly intermixed with the test trials to detect bias. The catch trials will be presented after every 30 trials for each of the tested spatial frequency at a contrast 10% above the current contrast for that spatial frequency; however, the catch trials will not be used to compute the threshold. Apart from the catch trials, no auditory or visual feedback will be used, as providing feedback is uncorrelated to the observer’s response (Herzog and Fahle, 1997; Bach and Schäfer, 2016).

A three-down one-up logarithmic staircase with dynamic steps is used to derive a contrast threshold with a level of accuracy of target detection of 79.4% on a psychometric function (Fernandes et al., 2019a). Initially, the contrast values appear at the suprathreshold level, for which we expect correct responses. After three consecutive correct responses, contrast decreases until an incorrect response. After every incorrect response, contrast increases. The Metropsis software computes the threshold after 12 contrast reversals have occurred at each spatial frequency. The order of the spatial frequencies is randomized within a session. Each stimulus has an exposure time of 600 ms. After responses were observed, the next trial starts after 300 ms. A higher CSF value indicates better discrimination (Figure 3). The CSF test can be performed in approximately 15–20 min.

**FIGURE 3 F3:**
[figure not shown]
Contrast sensitivity function task. The task was to identify, using a remote control response box, whether the gratings were presented on the left or right side of the computer screen. Each stimulus had an exposure time of 600 ms, with an intertrial interval of 300 ms. The Metropsis algorithm randomizes spatial frequencies (low, medium, and high) and contrast values.

#### Study 2—Cambridge Colour Test

The subject will be instructed to identify the orientation of the Landolt ring gap—presented randomized in one of the four positions [four-alternative forced choice (4-AFC)]—by pressing the corresponding button of the response box (CT6, CRS). If the location of the gap is not seen, then they should guess. The chromatic contrast of the Landolt ring varies relative to that of the background, using an adaptive staircase procedure (Figure 4). The specific rules are the chromatic contrast is halved (24%) after a correct response and doubled (48%) following an incorrect response or no response (within the allocated response time), until the first reversal, and 8% for the remaining reversals (in either direction). Periodically, a catch-trial target at maximum saturation is presented. It constitutes approximately 10% of the stimuli. Apart from the catch trials, no auditory or visual feedback will be used, as providing feedback is uncorrelated to the observer’s response (Herzog and Fahle, 1997; Bach and Schäfer, 2016). The test stops after six staircase reversals for each vector; chromatic contrast discrimination threshold (in *u*′*v*′ units) is computed as the average of the chromaticities corresponding to the six reversals. For each of the three confusion lines, the CCT algorithm implements two interleaved staircases presented in a random order using a weighted a one up/one down staircase rule, with a ratio of 1/3 to converge on the 75% threshold. Accuracy over speed will be emphasized in the instruction. The response box will be held by the participant with both hands, and the thumbs will be used for the button pressing. The time allowed for observers to respond will be 6 s. Both Trivector and Ellipse subtests should be completed by a participant in approximately 12 min (inside the peak concentration of nicotine).

**FIGURE 4 F4:**
[figure not shown]
Illustration of the chromatic targets **(A,B)**, Landolt “ring,” embedded in the luminance noise background. **(C)** Protan (P), deutan (D), and tritan (T) vectors in the CIE 1976 *u*′*v*′ chromaticity diagram. Reprinted from Fernandes et al. (2020) with permission from © The Optical Society.

### Pupil Effects

Because it was unclear as to whether the reduction in pupil size (Erdem et al., 2015) was due to nicotine or some other chemical in cigarette smoke, we carried out a pilot study (Columbus) on the effects of nicotine gum on pupil size. The main results indicated nicotine produced a small reduction in pupil size [baseline, 3.28 mm (± 0.24); 2-mg, 3.20 mm (± 0.17); and 4-mg, 3.15 mm (± 0.20)]. The change in pupil size is small. The maximum reduction in retinal illumination would be equivalent to a filter that transmits 92% of the light, which is relatively equal to the transmittance of a clear spectacle lens after accounting for light loss due to reflections. Based on these findings, we believe this reduction in retinal illumination is unlikely to affect the results.

### Statistical Analysis

For each study, the distribution of data will be assessed, including measures of central tendency and measures of dispersion. Distributions for each group will be compared using the Monte Carlo method for skewness and kurtosis, and the cutoff value will be ± 1.96, suggesting that departure from normality will not be observed (Antonius, 2003; Tabachnick and Fidell, 2007). We will both compare outcomes from skewness and kurtosis with the Shapiro–Wilk values. Data will be first plot or graph and then analyzed accordingly to the study. Statistical analysis will be performed using SPSS 25.0 and MATLAB R2018b^2^.

#### Study 1—Contrast Sensitivity Function

For the contrast sensitivity analysis, we will use a multivariate analysis of variance (MANOVA), with eight dependent variables (thresholds of each spatial frequency; continuous variables) and one independent, within-subject variable (condition ∼ three levels). *Post hoc* testing will be conducted using discriminant analysis.

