The retinal circuitry carries out early processing of luminous contrast (achromatic) and chromatic information. The information from the retina is relayed to the LGN via three different pathways on the basis of where they project into the LGN. The parvocellular pathway is believed to carry both luminous contrast information for fine detail along with chromatic information based on the long- (L) and middle- (M) wavelength sensitive cones. The magnocellular pathway relays luminous contrast information for low-contrast, coarse (or large) detail in their cells (Govind et al., 2009; Fernandes et al., 2018c). The koniocellular pathway carries chromatic information on the basis of the short (S) wavelength sensitive cone and both the M- and L-cone responses. The pathways are maintained from the LGN to the visual cortex, where the color and luminous contrast information is combined to provide the visual perception (Cornsweet, 2012). The majority of the nAChRs in the LGN are expressed in the parvocellular pathway, but nicotine also has an affinity for the magnocellular and koniocellular pathways (Govind et al., 2009). Acetylcholine and nicotinic inputs modulate some features of stimulus like orientation and direction (Sillito and Kemp, 1983; Roberts et al., 2005; Zinke et al., 2006).

Because nAChRs are present throughout the visual pathway, both basic chromatic and luminous contrast perception could be affected. Nevertheless, it is unclear as to whether the extent of these processes would be differently affected. The result that the majority of nAChRs are located within the parvocellular pathway suggests that color information along the red–green (L-cone—M-cone) dimension could be affected more than along the blue–yellow dimension (S-cone pathway), and contrast sensitivity for high spatial frequencies could be affected more than contrast sensitivity at low spatial frequencies. This hypothesis assumes that the net result of nicotine at the retinal level does not differentially affect the inputs into the three LGN pathways. However, it is unclear whether greater heterogeneity in the expression of retinal nAChRs subunits would play a role in these inputs. Our study attempts to investigate, without establishing a causal relationship, whether the achromatic and chromatic contrast discrimination will be differentially affected, for example.

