One needs to be careful when interpreting the outcomes of these two experiments because the nicotine may not have been at the peak concentration within the system. Varghese et al. (2011) tested individuals after 30 min of nicotine exposure. As reported by Russell et al. (1976), the peak occurs between 15 and 40 min, after the beginning of the chewing. Thus, conducting an experiment after 30 min of nicotine gum administration could be outside the peak concentration. Naser et al. (2011) did not report the time window. Other limitations include their sample sizes were small, and neither experiment used a blind, controlled design.

The two studies on nicotine and vision suggest that nicotine could enhance photopic vision; however, studies on smoking suggest that nicotine, or another component in tobacco smoke, could impair photopic visual processes slightly by decreasing the pupil size and thereby reducing retinal illumination (Kunchulia et al., 2014; Erdem et al., 2015).

The Effects of Nicotine Gum on Vision Administration (ENIGMA-Vis) is, to the best of our knowledge, the first randomized controlled clinical trial that aims to develop a framework to investigate the effects of nicotine gum on basic visual processing. Here, we discuss the rationale, methods, and design of our ongoing trial. The main aim is to test if individuals have improvements in early-stage visual processing from nicotine gum administration (Levin, 2001). The primary hypothesis guiding our trial is that individuals using higher doses of nicotine gum will show better visual processing. The secondary hypotheses are that (a) differences in visual performance are mediated by the body mass index (BMI), sex (e.g., metabolism for nicotine is different between males and females) but not for other demographic data (e.g., age); and (b) differences in visual performance are mediated by the serum cotinine concentration.

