## Methods and Analysis

### Aims

#### Study 1—Contrast Sensitivity Function

The first study will not be conducted simultaneously with the second study because it is a within-subject, and we cannot exclude the possibility of desensitization among individuals; therefore the participants enrolled in this first study will not participate in the second study. The primary aims for the contrast sensitivity function (CSF) measurements are investigating whether any of three conditions (placebo, 2-mg, or 4-mg doses) (a) influence visual performance for low, middle, and high spatial frequencies (ranging from 0.2 to 20 cycles per degree); (b) whether there is a dose dependency on contrast sensitivity; (c) whether BMI (we intend to select a pool of individuals with different BMIs) influence the results; (d) if there are differences related to sex; and (e) whether there is a serum cotinine concentration dependency of contrast sensitivity. Exploratory aims will test effects by age, height, weight, and years of education.

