#### Study 2—Cambridge Colour Test

The primary aims of this second study period are investigating whether any of three conditions (placebo, 2-mg, or 4-mg doses) (a) influence chromatic contrast discrimination for the S-, M-, and L-wavelength sensitive cones (blue, green, and red, respectively) using the Trivector subtest; (b) influence the position and direction (e.g., larger or more circular ellipses indicate worse discrimination) of an MacAdam chromatic discrimination ellipse for on an achromatic background (Ellipse 1); (c) determine whether there is a dose effect; (d) determine whether there is an interaction between the dosages and direction of the chromatic contrast discrimination; (e) are the results related to BMIs; (f) are different with regard to sex; and (g) determine whether there is an interaction between cotinine concentration and chromatic contrast discrimination. Exploratory aims will test effects by age, height, weight, and years of education.

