#### Study 2—Cambridge Colour Test

For the Trivector subtest of the CCT, we will use a one-way MANOVA, with three dependent variables (thresholds for protan, deutan, and tritan; continuous variables), and one independent, within-subject variable (condition ∼ three levels). For the Ellipse subtest, we will conduct a separate MANOVA for Ellipse 1 with two dependent variables (angle and area; continuous variables) and one independent, within-subject variable (condition ∼ three dosage). A moderation or mediation analysis (using 5,000 bootstrapping resamples) will be conducted to determine whether the area, length, angle, or ratio is a better predictor of any results of the CCT.

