### Anticipated Results

We expect, based on our hypothesis, that nicotine could lead to an improvement in visual processing, with the higher dose producing the largest improvement.

As observed in our past studies (de Almeida et al., 2018; Fernandes et al., 2018b,c; Silva et al., 2020), tobacco addiction resulted in early-stage visual processing impairments. However, smoking comes in the form of (i) smoke absorption and (ii) the consumption of numerous health-damaging compounds (nicotine is one of the numerous existing components) (Silva et al., 2020). In the mammalian brain, nAChR isoforms are expressed on mesolimbic and nigrostriatal neurons. Because about one-fourth of the brain is involved in visual processing and neurotransmitters such dopamine, GABA, and glutamate are also involved, it is not hard to explain that transient nicotine administration can have effects on vision (Balfour and Munafò, 2015). Note that the expression of nAChRs in the brain does not imply agreement of intakes = effects. This may be explained because the intake of nicotine gum is relative to the maximum amount and other factors such peak concentration, age, BMI, and gene expression (Benowitz, 2010; Balfour and Munafò, 2015). In light of these factors, our attempt is to control confounding factors and investigate the extent to which nicotine can improve vision.

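### The planned MANOVAs have condition as their only factor, so they test neither the dose-ordered primary hypothesis nor the dosage-by-direction interaction named as a Study 2 aim

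*Protocol article*

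**What the plan says.** **Hypotheses and aims.** The Introduction gives the primary hypothesis as "individuals using higher doses of nicotine gum will show better visual processing". Anticipated Results repeats the ordering, "with the higher dose producing the largest improvement". Under Aims, Study 1 asks whether the conditions "influence visual performance for low, middle, and high spatial frequencies" and "whether there is a dose dependency on contrast sensitivity". Study 2 lists a dose effect as aim (c), and aim (d) is to "determine whether there is an interaction between the dosages and direction of the chromatic contrast discrimination". The Introduction also expects that "contrast sensitivity for high spatial frequencies could be affected more than contrast sensitivity at low spatial frequencies", and that the red–green dimension could be affected more than blue–yellow.

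**Planned tests.** For Study 1, Statistical Analysis specifies a MANOVA on the thresholds at eight spatial frequencies, with condition (three levels, within-subject) as the only independent variable. Post hoc "testing will be conducted using discriminant analysis". For the Trivector data of Study 2, "we will use a one-way MANOVA, with three dependent variables" and again condition as the single within-subject factor. A separate MANOVA covers the angle and area of Ellipse 1. Study 2 names no follow-up comparing doses.

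**Decision rule.** Outcome Measures treats a 10% improvement at a frequency or on a colour-test parameter as meaningful, provided that a main effect or an interaction is significant.

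**The concern.** The questions are about order, direction and differential effect. The named tests are about whether any difference exists. With condition as the only factor and the frequencies or cone directions as dependent variables, the MANOVA asks whether some linear combination of outcomes differs between some of the conditions. It does not ask whether 4 mg exceeds 2 mg and 2 mg exceeds placebo, or whether the dose effect varies across directions.

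The follow-up does not fill the gap. Discriminant analysis gives loadings and a classification of sessions, not estimates of 2 mg or 4 mg against placebo. In its standard form it also treats the three sessions of one person as three independent observations.

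At stake is what a significant result would mean. It could be read as support for an ordered benefit when the data show another pattern, and the interaction that triggers the 10% rule would have to be defined after the results are seen.

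**Working it through.** **1. Aims against models**

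| Question in the article | Term needed | In the planned MANOVA? |
|---|---|---|
| Higher dose, better vision (primary hypothesis) | Signed dose contrast | No |
| Dose dependency (Study 1 aim b), dose effect (Study 2 aim c) | Dose contrasts | Only an unordered omnibus test |
| Dosage by direction (Study 2 aim d) | Condition × direction | No |
| High frequencies affected more than low (Introduction) | Condition × frequency | No |
| Interaction in the 10% rule | Any interaction | No |

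**2. Why the omnibus test carries no order.** The within-subject MANOVA is a Hotelling T² on 2p condition contrasts (p outcomes). Its power depends on λ = n·δ′Σ⁻¹δ, where δ holds the mean contrasts and Σ their covariance matrix. Replacing δ by −δ leaves λ unchanged, so benefit and harm of equal size are equally likely to reach significance.

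Simulation at n = 42 and alpha 0.01 (both from Sample Size). Assumed: unit SD, correlation 0.5 between outcomes, correlation 0.5/0.7/0.8 between conditions. Effects are in SD for placebo/2 mg/4 mg, the same on all outcomes.

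| Pattern | Omnibus, 8 outcomes | Omnibus, 3 outcomes |
|---|---|---|
| 0/0.2/0.4 (as hypothesised) | 0.14/0.31/0.52 | 0.31/0.58/0.84 |
| 0/−0.2/−0.4 (reversed) | 0.13/0.29/0.54 | 0.30/0.60/0.82 |
| 0/0.4/0 (2 mg only) | 0.22/0.47/0.74 | 0.44/0.75/0.95 |

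The first two rows differ only by simulation error. A one-sided paired linear dose contrast on the mean of the eight outcomes rejects 0.85/0.98/1.00 for the hypothesised pattern, 0.00 for the reversed pattern and about 0.01 for the third.

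**3. Why it does not isolate an interaction.** With eight outcomes the omnibus test rejects 0.14/0.31/0.52 for the uniform effect and 0.33/0.64/0.88 when only some outcomes respond. It reacts to both. A condition-by-outcome test stays between 0.008 and 0.014 for the uniform effect and rises to 0.37/0.70/0.92 for the selective one. With three outcomes its selective-effect power is 0.34/0.65/0.86.

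**4. Discriminant analysis in its standard, unpaired form.** With eight outcomes it rejects about 0.000 under the null, against a nominal 0.01, and 0.000 to 0.004 under the ordered effect. The error is conservative: it loses power and does not create false positives.

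**5. Would an averaged contrast be more powerful?** Take 4 mg minus placebo with a shift of 0.5 SD of the paired difference at k of 8 frequencies, 2 mg midway, and inter-frequency correlation r (shift and r assumed).

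- MANOVA: F(16, 26), λ = 42·[0.25/(1 − r)]·[k − r·k²/(1 + 7r)].
- Averaged contrast: noncentral t on 41 df, two-sided 0.01, standardised effect 0.5·(k/8)/√[(1 + 7r)/8].

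At r = 0.5, k = 8 gives λ = 18.7 and an effect of 0.667. At k = 4 they are 46.7 and 0.333.

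| Frequencies responding | MANOVA, r = 0.3/0.5/0.7 | Averaged contrast |
|---|---|---|
| 8 of 8 | 47/27/18% | 99/94/85% |
| 4 of 8 | 68/83/98% | 47/31/22% |

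The ranking reverses.

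**The case against.** **The full plan may hold the contrasts.** A journal article condenses, and contrasts, adjustments and intervals are often left to the SAP. This stands in part: their absence alone would be no finding. But the article does name the models and the follow-up, and it makes its relevance rule depend on an interaction that none of those MANOVAs contains. That mismatch is in the text.

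**Other stated rules might serve.** The 10% criterion is a relevance threshold, not a test. The Study 1 comparison with previously reported means (Material and Stimuli) is not a contrast with placebo. The regressions under Additional Analyses concern demographics and cotinine. None supplies the missing tests.

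A reader might also infer four stronger points, which the document does not support:

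- **That the analysis ignores the pairing.** Both MANOVAs are declared within-subject. Only the Study 1 follow-up could lose the pairing, and only if the standard form is used, which the article does not state.
- **That the MANOVA is generally underpowered.** This holds for a uniform shift. If high frequencies respond more, as the Introduction suggests, the MANOVA can have the higher power.
- **That dose-by-frequency is a named interaction aim.** Study 1 asks about effects at low, middle and high frequencies, and the differential effect is a hedged expectation. Only Study 2 aim (d) names an interaction.
- **That the trial could never say whether 4 mg beats placebo.** The paired data will exist. The gap is in pre-specification.

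**Conclusion.** The concern holds as a mismatch between stated questions and stated tests. The MANOVAs do not test the ordered primary hypothesis or Study 2 aim (d), give only an unordered answer on dose dependency, and cannot supply the interaction that the 10% rule mentions. This follows from the form of the models and needs no assumption about effects or correlations.

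The size does rest on assumptions. With eight outcomes, the omnibus test is about as likely to be significant for the reversed order as for the hypothesised one, and more likely when only 2 mg works. Those rates use the assumed SD pattern and correlations. The loss of pairing is conditional on standard discriminant analysis, applies to Study 1 only and is conservative. No general power advantage over MANOVA can be claimed.

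**What to change.** Before analysis, keep the within-subject MANOVA as an omnibus test if wished, and pre-specify:

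1. A paired linear dose contrast, and paired 4 mg and 2 mg contrasts against placebo. With equally spaced doses 0, 2 and 4 mg the linear weights are −1, 0, +1, so with complete data the linear contrast is the 4 mg minus placebo difference. The 2 mg contrast, or 4 mg against 2 mg, is therefore needed to speak to dose order.
2. A condition × direction test in Study 2 and a condition × frequency test in Study 1, with both factors within-subject.
3. Multiplicity-adjusted paired comparisons with confidence intervals at each frequency or direction, read against the plan's 10%.

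Label discriminant analysis descriptive, and tie the 10% rule under Outcome Measures to these named tests. Do not let an average over frequencies replace the per-frequency primary outcome; that changes what is estimated and loses power if the effect is selective.

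The cost is wording, a few more pre-specified tests and a multiplicity adjustment. The data collected do not change.
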